## 2.2 Objective

The objective of this trial (the Tina Trial) is to establish the effectiveness and safety of mirtazapine as an outpatient pharmacotherapy for methamphetamine use disorder in routine clinical practice in an Australian setting.

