| Depression (PHQ-9)                    | PHQ-9 score                                                                                                                                      |               | Median (IQR)      | 9 (4 - 13)               | 6 (3 - 10)             | 5 (2-9)                | 6 (2 - 9)              |
| Sleep (AIS-5)                         | AIS-5 score                                                                                                                                      |               | Median (IQR)      | 3 (0 -6)                 | 1 (0 - 3)              | 1 (0-3)                | 1 (0 - 4)              |
| HIV risk                              | HRBS score                                                                                                                                       |               | Median (IQR)      | 4 (2 - 8)                | 3 (1 - 6)              | 3 (1 - 6)              | 2 (1 - 6)              |
| Quality of life (EQ-5D)               | EQ-5D utility score                                                                                                                              |               | Median (IQR)      | 0.92 (0.85 - 0.97)       | 0.93 (0.85 - 1.00)     | 0.93 (0.85 - 1.00)     | 0.93 (0.89 - 1.00)     |
| Tertiary/exploratory outcomes: |                                                                                                                                                  |               |                   |                          |                        |                        |                        |
| Other substance use                   | Total days use for other drug classes (tobacco, alcohol, cannabis, cocaine, ecstasy, hallucinogens, inhalants, and heroin) in the past 28 days   |               | Mean (SD)         | 34 (20)                  | 31 (28 - 49)           | 31 (28 - 46)           | 30 (28 - 49)           |
| Suicidality                           | Score of 3 or more on the CSSRS-S since the previous assessment                                                                                  |               | n (%)             | 0 (0)                    | N/A                    | N/A                    | 11 (4)                 |

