## 5 Statistical Principles and definitions

### 5.1 Confidence intervals and p values

All tests will be two-tailed. Significance will be  $p < 0.05$  for all outcomes. Confidence intervals will be 95%.

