## 6.4 Planned analysis of the tertiary and exploratory outcomes

Planned analyses of the tertiary outcomes of other substance use, anxiety, and patient impression will be based on the unimputed intention-to-treat dataset.

Other substance use: The effect of the trial medication on days of other substance use will be tested using a mixed model with a group (placebo [0] vs. mirtazapine [1]) by time (baseline [0], week 4 [1], week 8 [2], week 12 [3], week 20 [4]) interaction effect, with time entered as a factor variable, producing individual effect estimates for each time point and making no assumptions about the linearity of changes over time. The primary timepoint is week 12. A generalised linear mixed model will be used to test this effect.

Anxiety: The effect of mirtazapine on anxiety will be tested using a mixed model using a group (placebo [0] vs. mirtazapine [1]) by time (baseline [0] vs. weeks 4 [1], week 8 [2] and 12 [3]) interaction effect, with time entered as a factor variable, producing individual effect estimates for each time point and making no assumptions about the linearity of changes over time. The primary timepoint is week 12. A generalised linear mixed model will be used to test this effect.

Patient impression: The effect of mirtazapine on the PGI scale score will be tested a group contrast (placebo [0] vs. mirtazapine [1]) across all follow-up time points (weeks 4, 8 and 12) to obtain an average treatment effect across the 12-week intervention period. A generalised linear mixed model will be used to test this effect.

Adverse events: The analysis of adverse event data will be based on the safety dataset and include only adverse event data for the 12-week trial medication period (wk 0 to wk 12). The percentage of participants reporting adverse events and serious adverse events for each System Organ Class will be compared between conditions using a Pearson's Chi-Square test. For serious adverse events, expectedness and causality will be reported.

Suicidality: The analysis of suicidality will be based on the safety dataset and include only suicidality data for the 12-week trial medication period (wk 0 to wk 12). The percentage of participants who screened positive for suicide risk (CSSRS-S score of 3 or greater) during the 12-week trial medication period (wk 0 to wk 12) will be compared between conditions (placebo [0] vs. mirtazapine [1]) using a Pearson's Chi-Square test.

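### Section 6.4 compares suicidality and adverse events by chi-square test alone, so a non-significant safety result would carry no bound on the excess risk

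*Combined protocol and SAP*

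**What the plan says.** Section 2.2 gives the aim as "to establish the effectiveness and safety of mirtazapine as an outpatient pharmacotherapy for methamphetamine use disorder". Section 6.4 then sets out the between-arm safety analyses, restricted to the 12-week medication period and the safety dataset:

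- Suicidality: the share of participants scoring 3 or more on the CSSRS-S "will be compared between conditions (placebo [0] vs. mirtazapine [1]) using a Pearson's Chi-Square test".
- Adverse events and serious adverse events: the share of participants affected "for each System Organ Class will be compared between conditions using a Pearson's Chi-Square test". Expectedness and causality are also reported for serious events.

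Neither item names a risk difference, risk ratio, confidence interval or upper limit. Section 5.1 makes all tests two-tailed at p < 0.05 "for all outcomes. Confidence intervals will be 95" per cent, which fixes a level without saying which safety quantity gets an interval. The primary outcome, by contrast, has a defined rate ratio in section 6.2. Section 3.3 states power for methamphetamine use days only.

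Table 6 describes the suicidality measure as "Score of 3 or more on the CSSRS-S since the previous assessment" and shows 11 (4%) in the week 12 column, with no entry at weeks 4 and 8. Its values are marked as indicative. Section 5.4 defines the analysed outcome differently, as a positive score at any time from week 0 to week 12. Section 5.4 also lists adverse events among the outcomes with no planned analysis, which does not agree with the test in 6.4.

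**The concern.** A chi-square test returns a p-value. It does not say how large the difference is or how large a harm remains compatible with the data. With few events a non-significant result is likely even under a substantial excess, so it says little about safety. What the reader needs is the size of the excess risk that has not been ruled out, and the plan does not undertake to report it.

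This matters most for suicidality. The exclusion criteria list suicide among the high-risk reactions, and the CSSRS-S is given at every main assessment. If the estimate and interval are not specified before unblinding, they are either left to the reader or chosen after the result is known.

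**Working it through.** **The plan's own figure.** Week 12 has 293 assessments, 3 of them without a CSSRS-S (Table 4), leaving 290. 11/290 = 3.8% and 11/293 = 3.8%, both printed as 4%. 11/319 = 3.4% would print as 3%. The 4% therefore uses week 12 attenders as its base, and positives among people who left earlier may not be in the 11.

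**Inputs.**
- Safety set: 339 treated minus 20 with no assessment after baseline (section 4.2) = about 319.
- Arm sizes: taken as 160 (mirtazapine) and 159 (placebo). This is an assumption, from 1:1 allocation and blinded data.
- Events: 11, if Table 6 gives the 12-week total (assumption).

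**Pearson chi-square without continuity correction**, N(ad - bc)² / (n1 n2 m1 m2), where m1 and m2 are the totals with and without an event:
- 8 v 3: 319 × (8×156 - 152×3)² / (160×159×11×308) = 319 × 792² / 86,190,720 = 2.32, p = 0.128. Risk ratio = (8/160)/(3/159) = 2.65.
- 9 v 2: 319 × (9×157 - 151×2)² / 86,190,720 = 319 × 1,111² / 86,190,720 = 4.57, p = 0.033. Risk ratio = 4.47. Fisher's exact test gives 0.061.

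So 8 v 3 is the largest non-significant imbalance at 11 events. Other denominators change little: for 8 v 3, p = 0.124 with 145 v 145, 0.127 with 147 v 146, and 0.128 with 170 v 169.

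**Newcombe 95% interval for 8/160 v 3/159.** The Wilson limits are 2.56% to 9.56% around 5.00%, and 0.64% to 5.40% around 1.89%. The difference is 3.11 points.
- Lower: 3.11 - √[(5.00 - 2.56)² + (5.40 - 1.89)²] = 3.11 - 4.28 = -1.2.
- Upper: 3.11 + √[(9.56 - 5.00)² + (1.89 - 0.64)²] = 3.11 + 4.72 = +7.8.

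The score interval for the risk ratio is 0.78 to 9.1.

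**If the 12-week total is not 11** (same arm sizes):

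| Events | Largest non-significant split | Risk ratio | p |
|---|---|---|---|
| 11 | 8:3 | 2.65 | 0.128 |
| 12 | 9:3 | 2.98 | 0.079 |
| 15 | 11:4 | 2.73 | 0.066 |
| 18 | 13:5 | 2.58 | 0.054 |
| 20 | 14:6 | 2.32 | 0.067 |
| 22 | 15:7 | 2.13 | 0.080 |

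The sequence is uneven because counts are whole numbers; at 21 events the ratio is 1.99. At 20 events a 15:5 split (ratio 2.98) is significant: 319 × (15×154 - 145×5)² / (160×159×20×299) = 5.27, p = 0.022.

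**Power for context.** At a pooled rate of 11/319, exact power is 0.19 for a true doubling (2.3% v 4.6%) and 0.39 for a true tripling (1.7% v 5.2%).

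**Adverse-event classes.** The SAP gives no counts, so any rates are assumed. On the same arm sizes the test would miss 1% v 3% about 77% of the time, 5% v 10% about 60%, and 30% v 45% about 21%. These only illustrate how the answer depends on the assumed rates.

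**The case against.** Several points on the other side have weight.

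A reader might infer that a near-threefold excess of suicidality would be reported as no difference. The SAP does not support that. No section equates p > 0.05 with no difference or with safety, and the arm percentages would be printed, so 5.0% against 1.9% would be visible. What can be said is that the result would be non-significant and that no bound is planned. The near-threefold figure is also conditional: at 20 events a ratio of 2.98 would be significant.

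Section 6.1 offers a logistic link for categorical outcomes, allows a Poisson or negative binomial link where cells are small, and provides for changing models after unblinding. Such models would give ratios with intervals. But section 6.4 names a specific test for these outcomes, and the general text does not replace it.

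The trial was sized for methamphetamine use days, section 2.3 has no safety hypothesis, and suicidality is tertiary. Low power for rare harms is therefore inherent, and an interval does not change it. That stands, and it is why the miss rates are not the argument here. The argument is that a p-value alone does not show how little has been excluded.

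A reader could compute an interval from the percentages and arm sizes. That is true, but where safety is part of the objective the report should supply it. Finally, the text reviewed is the SAP. Section 6.7 says that exploratory analyses are detailed in the separate protocol, and the Appendix classes adverse events as exploratory, so further safety analyses there cannot be excluded.

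**Conclusion.** The concern holds in limited form. For an objective that includes safety, section 6.4 makes a chi-square p-value the only named inferential output for suicidality and for adverse and serious adverse events, with no effect measure or interval. For suicidality, an 8 to 3 split would give p = 0.13 with nothing reported to show that an excess of up to 7.8 points is compatible with the data. That figure assumes that 11 is the complete 12-week count and that the arms are about 160 and 159. With 15 to 22 events, the largest non-significant ratio lies between about 2.0 and 2.7. No equivalent figure can be given for adverse events, because the SAP shows no counts for them. The primary efficacy analysis is unaffected.

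**What to change.** Before unblinding, amend section 6.4 as follows:

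- Make the risk difference (mirtazapine minus placebo) with a 95% score-type interval, Newcombe or Miettinen-Nurminen, the main safety estimate for suicidality, any adverse event, any serious adverse event and each System Organ Class.
- Keep the p-value as secondary, using an exact test where an expected count is below 5. At 11 suicidality events the smallest expected count is 11 × 159/319 = 5.48, so the chi-square test would stay in use there.
- State that safety conclusions rest on the interval, including its upper limit, and not on non-significance. No fixed margin is needed.
- Say whether the Table 6 suicidality count is cumulative over weeks 0 to 12 and whether it includes people who left before week 12. Reconcile the placing of adverse events in section 5.4 with the analysis in 6.4.

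The cost is SAP wording and extra columns in the safety tables, with no new data or participants. The intervals for suicidality and serious events will probably be wide, so the safety statement will be more cautious. The change makes that uncertainty visible but does not increase the power to detect harm.

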## 6.5 Sensitivity analyses

Sensitivity analyses will be conducted that imputes missing data for the analyses of the primary outcome of methamphetamine use days and for the secondary outcome of methamphetamine abstinence.

Sensitivity analysis may be conducted to test the assumption that the data are not missing at random for the primary outcome of methamphetamine use days and for the secondary outcome of methamphetamine abstinence. This will involve testing the impact of different assumed outcome values for missing data on the final treatment effect estimate.

## 6.6 Additional analyses

The following analyses may be done after the primary analysis to supplement the primary analyses or as separate research papers.

Subgroup analyses: Subgroup analyses are planned for the sub-groups of (1) depressed (PHQ-9 score 10 or greater at eligibility), (2) not depressed (PHQ-9 score of < 10 at eligibility), (3) participants who reported being male at birth, and (3) participants who reported being female or other sex at birth. The randomisation was stratified on these subgroups, meaning that participants are randomly assigned to condition within each subgroup.

Per-protocol analysis: A set of per-protocol analyses will be undertaken on the per-protocol dataset. This may be done for the primary and secondary end-points and for any sub-group analyses. The per protocol analysis will use non-imputed data. These models will incorporate adjustment to account for any group differences in baseline characteristics.

Treatment complier effect: A set of treatment complier analyses may be conducted on the treatment complier dataset. This may be done for the primary and secondary endpoints and for any sub-group analyses. Treatment complier analysis will incorporate adjustment to account for any group differences in baseline characteristics.

Average treatment effect: Additional analyses may be conducted that repeat the primary and secondary analyses but which collapse the follow-up data across the week 4, 8 and 12 follow-up time points (i.e., baseline [0] vs. week 4 [1], week 8 [1], week 12 [1]) such that the outcome is the average treatment effect across the 12-week trial medication period.

Covariate adjustment. Analyses of the primary outcome measure will be repeated with adjustment for a set of prognostic variables, as per the recommendations of Kahan et al. [32], to improve model precision and aid interpretation of the main analyses of the primary outcome. These prognostic variables will include: age, sex (male vs. female or other), methamphetamine use days in the past 4 weeks at eligibility, main route of methamphetamine administration (injecting vs. other routes), and PHQ-9 depression score at eligibility. All of these variables were collected at the eligibility assessment, prior to randomisation, and therefore they are not collider variables.

## 6.7 Exploratory analyses and embedded studies

Exploratory analyses that have been planned to-date are detailed in the protocol. No statistical analysis plan has been developed for these exploratory analyses. Nor have any other exploratory analyses had been planned at the time of writing this Statistical Analysis Plan.

If the intervention is effective, cost analyses will be undertaken. These will be detailed in a subsequent Health Economic Analysis Plan. Data collected to facilitate this analysis include: (1) the EQ-5D-5L[22] version 2.1 (2) the Work Productivity and Activity Impairment Questionnaire – General Health V2 (WPAI-GH), and (3) data on health service utilisation and criminal justice contact.

## 6.8 Missing data

Missing data will be imputed using multiple chained equations (fully conditional specification) in R. For imputed data on days of methamphetamine use in the past four weeks, the exposure time (offset) for any missing periods will be set at 28 days. Imputation models will include days of methamphetamine use in the past 28 days at the baseline assessment and any data on days of methamphetamine use from the observed follow-up assessments. For imputed data on

methamphetamine negative oral fluid samples, the number of assessments where oral fluid test results were missing will be included. Other variables related to attrition will be considered for inclusion in the imputation model. Based on Monte-Carlo error, the number of imputations used will be based on the percentage of cases with missing data, rounded up to the nearest 10 (e.g. for 15% missing data, M=20 imputations will be used [33]).

If adequate imputation models cannot be derived, the alternative strategy will be to use Inverse Probability of Censoring Weighting (IPCW) to adjust for differences between groups in baseline for baseline variables that are correlated with missingness.

Details of any imputation models will be included in online supplementary material on publication.

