# 3 Study methods

## 3.1 Trial design

The Tina Trial is a multi-site double-blind randomised placebo-controlled parallel group, two arm, superiority trial with a 1:1 allocation ratio.

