## 3.3 Sample size

The estimated sample size required for the study (N = 340; 170 per group) was to enable us to detect a minimum rate ratio of 0.75 on our primary outcome (equivalent to a relative reduction from 25 days methamphetamine use in the past 4 weeks at baseline to 20 days use in the past 4 weeks at week 12) with 90% power (two-tailed test,  $p = 0.05$ ). This sample size calculation was based on the effect size found in the most recent trial of mirtazapine for methamphetamine dependence [15] and allows for up to 25% attrition (ie., a final sample of at least 255, or 128 per group, at week 12).

We randomised 344 participants in the trial, of whom 339 participants received the trial medication and 293 completed their week 12 assessment, meeting the sample size requirements estimated above.

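### The imputation predictors listed in section 6.8 omit randomised arm, so the imputed sensitivity analyses would shrink any true treatment effect by roughly 9–14% on the log scale

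*Combined protocol and SAP*

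**What the plan says.** Section 6.5 commits to imputed analyses of days of use and of abstinence: "Sensitivity analyses will be conducted that imputes missing data for the analyses of the primary outcome". A not-at-random analysis is optional there, so imputation is the only missing-data sensitivity analysis that the SAP promises.

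Section 6.8 describes chained equations and names the predictors. For days of use: "Imputation models will include days of methamphetamine use in the past 28 days at the baseline assessment", together with days from whichever follow-up assessments were observed. For oral fluid, the count of assessments with no test result is added. Beyond these, "Other variables related to attrition will be considered for inclusion in the imputation model". Neither section names arm as a predictor or says that imputation is done by arm.

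The analysis models do contain arm. Section 6.2 tests a group-by-time interaction on days of use, with week 12 as the primary time point. Section 6.3 tests abstinence as a group contrast averaged over weeks 4, 8 and 12. Sections 6.2 and 6.3 base the primary and secondary analyses on unimputed data.

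**The concern.** An imputation model should contain every variable whose effect the analysis model estimates. If arm is left out, missing values are drawn from a relation fitted to both arms together. The completed data then mix observed outcomes that differ by arm with imputed outcomes that differ by arm less than they should, and the estimate moves towards a ratio of 1. This happens even when the data are missing completely at random, because it depends on arm predicting the outcome and not on arm predicting dropout. A rule that admits variables for their relation to attrition therefore screens on the wrong property.

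At stake is how the sensitivity analysis is read. If the trial shows an effect, the imputed estimate would come out weaker by construction, and readers could take that as fragility to missing data.

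**Working it through.** **The plan's own attrition figure.** Section 3.3 sizes the trial "to detect a minimum rate ratio of 0.75 on our primary outcome" and "allows for up to 25% attrition (ie., a final sample of at least 255, or 128 per group, at week 12". Check: 255 / 0.75 = 340, which matches the stated total. Per group, 128 / 0.75 = 170.7, so 171 against 170 stated, which is rounding. The stated 90% power cannot be reproduced because no dispersion is given; nothing below depends on it.

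**Inputs from the documents**
- Days of use (Table 3, of 339): observed 315, 300 and 293, so 24 (7.1%), 39 (11.5%) and 46 (13.6%) missing at weeks 4, 8 and 12. The text of section 4.7 gives 292 at week 12; using it gives 47 / 339 = 13.9%.
- No assessment after baseline (section 4.2): 20 of 339 (5.9%).
- Oral fluid (Table 3): 871 samples of 1,017, so 146 (14.4%) missing over the three visits.
- "superiority trial with a 1:1 allocation ratio" (section 3.1).

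**Step 1: closed-form ceiling for days of use.** Suppose that imputed week-12 values carry no arm information, missingness is equal in the arms, and baseline is balanced. With missing fraction f and true ratio RR (placebo mean set to 1), imputed values average (1 + RR)/2 in both arms:

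RR* = [(1 − f)·RR + f·(1 + RR)/2] / [(1 − f) + f·(1 + RR)/2]

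For f = 46/339 = 0.1357 and RR = 0.75:
- active: 0.8643 × 0.75 + 0.1357 × 0.875 = 0.767
- placebo: 0.8643 + 0.1357 × 0.875 = 0.983
- RR* = 0.780; loss of log effect = 1 − ln 0.780 / ln 0.75 = 13.7%

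For RR = 0.80 the same formula gives 0.825.

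**Step 2: simulation with the listed predictors.** Observed follow-up days carry some arm information, so the loss can fall below the ceiling. Trials of 339 were simulated with the missing counts above, including the 20 with no follow-up, and a true ratio of 0.75. Imputation was by chained Bayesian linear regressions on baseline and the other follow-up weeks, with and without arm. The estimate was the ratio of mean change from baseline, active over placebo. Assumptions not in the documents: data missing completely at random, SD 8 days, placebo means 22, 19, 18.5 and 18 days, and three shapes of effect over time. There were 400 trials per cell and 4 imputations each. Cells show the ratio without arm / with arm, then the share of the log effect lost by leaving arm out.

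| Effect over time | Correlation 0.3 | Correlation 0.5 | Correlation 0.7 |
|---|---|---|---|
| Constant from week 4 | 0.773 / 0.749, 11.3% | 0.772 / 0.750, 10.1% | 0.773 / 0.753, 9.1% |
| Gradual | 0.778 / 0.750, 12.8% | 0.781 / 0.754, 12.1% | 0.776 / 0.750, 11.8% |
| Week 12 only | 0.779 / 0.750, 13.5% | 0.778 / 0.748, 13.7% | 0.781 / 0.752, 13.6% |

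Monte Carlo standard error of the loss is about 0.3 percentage points or less.

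**Step 3: a second, differently built simulation.** Days were bounded at 0–28, medians set close to Table 6, imputation was by predictive mean matching, and visit correlations were about 0.5–0.56 (assumed). It counted two wholly inpatient windows as missing at weeks 8 and 12. A ratio of 0.751 in the full data became 0.776 without arm and 0.750 with arm; 0.800 became 0.823 and 0.799.

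**Step 4: abstinence.** This was not simulated. As an illustration only, assume negative rates of 10% and 15% (the pooled interim figures in Table 6 are 11–14%) and imputed results with no arm information, averaging 12.5%. With f = 0.144:
- higher arm: 0.856 × 0.15 + 0.144 × 0.125 = 0.146
- lower arm: 0.856 × 0.10 + 0.144 × 0.125 = 0.104

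The odds ratio moves from 1.59 to 1.48, about 15% of the log effect. If the imputation uses predictors that carry arm information, the loss is smaller.

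**The case against.** The strongest reply is that section 6.8 gives a minimum list, not a closed one. It does not forbid arm, section 6.1 lets models be modified after unblinding, and details of the imputation models are promised on publication. The SAP was also written on data without the allocation variable. This much stands: the text is silent on arm and does not exclude it. But the only entry rule that it states is relation to attrition, which need not admit arm, and adding arm later would be a choice made after unblinding.

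It is also fair that only supporting analyses are affected, that the bias is modest, and that it vanishes if there is no true effect.

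Four stronger readings are tempting and are not supported:
- **That every imputed value assumes no effect.** Observed follow-up days carry some arm information; only the 20 participants with no follow-up contribute none.
- **That significance would be lost.** Section 5.1 fixes the test ("All tests will be two-tailed. Significance will be" 0.05). The design implies a standard error of |ln 0.75| / (1.960 + 1.282) = 0.0887, but for 255 evaluable. Scaled to 293 it is 0.0887 × √(255/293) = 0.083. A ratio of 0.83, itself chosen near the threshold, then has p = 0.024, and about 0.048–0.050 after a 12% loss. That does not clearly cross, and the base standard error cannot be verified.
- **That 48 are missing at week 12, or that 17.7% is the fraction for abstinence.** Two of the 48 are windows censored by design. The 17.7% (60 of 339) is week 12 alone, while abstinence is averaged over three visits.
- **That the weighting fallback has the same fault.** The phrase "Inverse Probability of Censoring Weighting (IPCW) to adjust for differences between groups in baseline for baseline variables" could mean balancing the arms, but the sentence is unclear, does not define its groups, and refers to variables correlated with missingness. It needs clearer wording; it is not a demonstrated error.

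**Conclusion.** The concern holds in this form: the stated imputation specification is deficient because it omits arm, and followed as listed it biases the imputed sensitivity analyses towards no difference when a true effect exists. For days of use the size is 0.75 estimated as about 0.77–0.78, a loss of roughly 9–14% of the log effect. It is smallest with a constant effect and high within-person correlation, and largest when the effect appears only at week 12. These figures rest on assumed correlations and variances and on data missing completely at random. For abstinence the direction is the same, with 14.4% of samples missing; the illustrative figure rests on assumed rates and is not an estimate for this trial.

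The primary and secondary conclusions do not depend on this. It should be corrected because the committed sensitivity analysis would otherwise lean against the effect whose robustness it is meant to test.

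**What to change.** In section 6.8, state that imputation is carried out separately within each arm, or that arm, with arm-by-time, is in every imputation model whatever its relation to attrition. With one equation per visit, arm as a predictor in each equation achieves the latter. Say that this applies to both days of use and oral fluid results. The weighting sentence can be reworded at the same time to say what is being modelled and which groups are meant.

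The cost is about two sentences of SAP text, no new data and negligible analyst time. The SAP was written on blinded data; the documents do not show whether unblinding has since occurred. The change is best made before it, and otherwise dated and recorded as an amendment.
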